### Data analyses

Hierarchical regression analyses with a three-level structure [38] will be conducted to explore the effects of the SW-PBIS on study outcomes. Hierarchical regression analyses allow to account for the nested structure of the data, in which teachers’ and students’ responses are nested within schools and grade levels. The outcomes at school and individual level will be studied as a function of time (three time points for wave 1 and two time points for wave 2) and group belonging (intervention or control group). To take into account the nestedness of the data, three-level random effect model will be used, varying by school, grade and the individuals’ identification codes. Furthermore, the possible mediators (quality of implementation) and moderators (school characteristics, school-level variables) of the SW-PBIS intervention will be analyzed. Missing data will be handled by imputation, provided that the assumption of data missing completely at random is met.

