## Methods: participants, interventions and outcomes

This study includes two waves of participant recruitment with two designs: quasi-experimental non-randomized design (wave 1) and cluster-randomized design (wave 2). The intervention study has been approved by the Swedish Ethical Review Authority (2022-03482-01), and registered as a clinical trial at www.clinicalTrials.gov (identifier NCT06270914). The choice of two waves of recruitment is motivated by the challenge to retain a control group over two years, as previous studies have implemented SW-PBIS for three to four years [16, 18]. Therefore, two waves of recruitment are used. In the first wave of recruitment, intervention and active control group are used and outcomes will be measured at three time points. In addition to quantitative data, qualitative observations and interviews are conducted to get a deeper understanding of the process of implementation of SW-PBIS. In the second wave of data recruitment, intervention and wait-list control group are used and outcomes will be measured at two time points (pre- and post). In Fig. 1, recruitment and data collection for both waves of data collection are described.

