### Participants

The study will be conducted in compulsory schools and include classes from grade one to grade nine. Inclusion criteria for the intervention and control groups are: (a) compulsory school, grades 1–9; (b) the school have not been previously enrolled in an SW-PBIS program by other providers (b) principal, teachers, students and their parents consent to participate in the study. Each of the two waves of recruitment in the study will include 80 schools. According to estimations with the software Optimal Design [25], 62 schools are required, based on an effect size of 0.25 and a power of 80%, with an expected amount of 12 classes per school, 20 students per class and an intraclass correlation (ICC) of 0.10 at school level and 0.05 at classroom level [26]. To account for 20% attrition, 80 schools are needed. Based on previous studies of SW-PBIS in the European context [14, 32], we expect Cohen’s d effect size of 0.20 to measure an important difference between the intervention and control group.

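### For the randomised wave 2, the stated model in time and group reads most naturally as a comparison of change; adjusting for or constraining the baseline is more precise, and a school-by-time term should be explicit

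*Protocol article*

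**What the plan says.** The Methods section describes a "quasi-experimental non-randomized design (wave 1) and cluster-randomized design (wave 2"). In wave 2, "intervention and wait-list control group are used and outcomes will be measured at two time points (pre- and post"). Table 1 lists the wave 2 measures (teacher-rated skills, learning environment, collective self-efficacy, problem behaviour) in 2024 and again in 2025.

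The Data analyses section gives one model for both waves. Outcomes are a function of time ("two time points for wave 2) and group belonging (intervention or control group"), and a "three-level random effect model will be used, varying by school, grade and the individuals" is named for the nesting. The baseline therefore enters as a repeated response. The section does not mention the baseline as a covariate, a common baseline mean across arms, or a school-by-time effect. It allows imputation of missing data only if they are missing completely at random.

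The Participants section plans on an effect of 0.25 with 80% power, 12 classes per school, and "20 students per class and an intraclass correlation (ICC) of 0.10 at school level and 0.05 at classroom level", giving 62 schools before attrition. It then names 0.20 as the expected effect.

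**The concern.** In a model of time and group with two occasions, the term that carries the intervention effect is the time-by-group interaction. A group main effect averaged over pre and post would dilute the effect. With complete data, the interaction is the difference between arms in mean change.

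Randomisation makes that contrast valid but does not make it the best use of the pre-test. Subtracting the full baseline adds its noise to the contrast, whereas regression on the baseline removes only the part that predicts the post-test. The choice has to work at school level, because nearly all the variance of the contrast lies there.

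The random part raises a second question. Intercepts for school, grade and individual cancel from a change contrast. If nothing else is fitted, differences between schools in how much they change, which dominate the true sampling error in a school-randomised design, go into the residual as if they were independent pupil noise.

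**Working it through.** **Inputs from the Participants section.** ICC 0.10 (school) and 0.05 (class), 12 classes of 20 pupils, 62 schools, effects of 0.25 (planning) and 0.20 (expected).

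**Assumed, because not stated.** Two-sided 5%, 1:1 allocation, equal pre and post variances, pre-test unaffected by allocation, and r from 0.3 to 0.9.

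**The plan's own figure.** Variance of a school mean: V = 0.10 + 0.05/12 + 0.85/240 = 0.1077, of which 0.10/0.1077 = 93% is between schools. For a post-test comparison without a covariate, effect 0.25 and 80% power, this gives 56 schools (normal) or 57 (t). The stated 62 is not reproduced; it is about 9% conservative and gives 83.9% power.

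**Relative variances.** Post-test alone 1; change 2(1 - r); baseline-adjusted 1 - r². Change over adjusted: 2(1 - r)/(1 - r²) = 2/(1 + r), which exceeds 1 for every r below 1. For r below 0.5, change is less precise than the post-test alone.

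**Power with 62 schools.** SE = sqrt(4 × 0.1077 × factor / 62), non-central t with 60 df (59 with the covariate). Example at r = 0.5 and effect 0.20: change has factor 1.00, SE 0.083, power 66%; adjusted has factor 0.75, SE 0.072, power 78%.

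| r | variance ratio | effect 0.20: change v adjusted | effect 0.25: change v adjusted |
|---|---|---|---|
| 0.3 | 1.54 | 51% v 70% | 70% v 87% |
| 0.5 | 1.33 | 66% v 78% | 84% v 93% |
| 0.7 | 1.18 | 86% v 91% | 97% v 98.5% |
| 0.9 | 1.05 | both near 100% | both near 100% |

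Schools needed for 80% power at 0.25, change v adjusted: 78 v 52 (r = 0.3), 57 v 43 (0.5), 35 v 30 (0.7). The covariate costs one degree of freedom; taken alone, that moves power from 83.91% to 83.89%.

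**Check by generalised least squares.** With a school-level correlation of 0.5, and 0.6 assumed for class and pupil, the SE is 0.083 for the unconstrained time-by-group model and 0.072 with a common baseline mean. At 0.7 it is 0.065 and 0.060.

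**If the random effects are intercepts only.** Same correlations, school level 0.5.
- True variance of a school's mean change: 2 × (0.10 × 0.5 + 0.05 × 0.4/12 + 0.85 × 0.4/240) = 0.1062. True SE = sqrt(4 × 0.1062/62) = 0.083.
- Residual variance that the model sees: 0.05 + 0.02 + 0.34 = 0.41, so 0.82 per pupil change, with 31 × 240 = 7,440 pupils per arm. Model SE = sqrt(2 × 0.82/7,440) = 0.015.
- A nominal 5% test would then reject a true null with probability P(|Z| > 1.96 × 0.0148/0.0828), about 73%.

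**The case against.** **The article does not write this model out.** It names no interaction, change score or arm-specific baseline means. A constrained-baseline model is itself a mixed model in time and group, so the wording does not exclude the remedy. This stands: the change contrast is the natural reading, not the literal text.

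**The random-effects complaint is conditional.** Naming school, grade and individual lists grouping levels; it does not say intercepts only. A reader might infer that the wave 2 standard errors will be wrong. The documents do not support that; they support only that the errors would be wrong under that specification.

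**Such detail often sits in an analysis plan.** That is so, but the article states both the fixed and the random part of the model, and the point concerns what those would estimate.

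**Both estimators are valid under randomisation, and the size is uncertain.** This stands. The issue with the contrast is precision, not bias. The correlation r is not in the documents, and the gain nearly vanishes as r approaches 1. At the planning effect of 0.25, change still meets the 80% target for r of 0.5 or more. Part of the shortfall at 0.20 comes from planning on 0.25 while expecting 0.20, which is a separate matter.

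**Adjustment is not entirely free.** A post-test model with the baseline as covariate drops pupils without a baseline unless it is imputed, and the plan restricts imputation.

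**Chance-only baseline differences are assumed.** The article does not say whether the wave 2 pre-test precedes allocation, and teachers rate pupils' skills.

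**Conclusion.** The point holds as a recommended improvement to wave 2. On the natural reading of the Data analyses section, the planned contrast is less precise than a baseline-adjusted or constrained-baseline analysis of the same data for every r below 1. The loss is material at low to moderate r (12 points of power at r = 0.5 and effect 0.20) and small at high r. This rests on equal pre and post variances, a pre-test unaffected by allocation, and the assumed test level and allocation ratio.

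If the listed effects are intercepts only, the consequence is more serious than lost precision: a standard error of about 0.015 against a true 0.083 at r = 0.5, and a test that rejects far too often. Because the text leaves this open, it is something to settle rather than a demonstrated error.

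A reader might go further and conclude that the change analysis is biased, or that wave 2 is underpowered because of it. Neither follows: the change contrast is unbiased under randomisation, and its power depends on a correlation that the documents do not give. Nor does the argument carry over to wave 1, where allocation follows the principals' choice and equal baselines cannot be assumed.

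**What to change.** For wave 2 only, name one of these as the main analysis:

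- a longitudinal mixed model with baseline means constrained equal across arms and a school-by-time random effect; or
- a post-test mixed model with group, the pupil's baseline score and the school's baseline mean as covariates, and a random school effect. The school mean is needed because most of the variance lies between schools.

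The first keeps pupils without a baseline; the second loses them unless the baseline is imputed. If an unconstrained time-by-group model is kept, include a school-by-time random effect. State whether the wave 2 pre-test is completed before allocation is known. Keep wave 1 as a separate analysis.

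The cost is wording: the pre-test is already scheduled and no further data are needed.

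### The named random effects (school, grade, individual) include no school-by-time term and no class level; fitted as random intercepts, they leave the group-by-time test blind to school clustering of change

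*Protocol article*

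**What the plan says.** All references are to the protocol article.

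- **Random part (Data analyses).** A "three-level random effect model will be used, varying by school, grade and the individuals", the individuals being identified by their codes. The stated reason is that "responses are nested within schools and grade levels".
- **Fixed part (Data analyses).** Outcomes "will be studied as a function of time (three time points for wave 1 and two time points for wave 2) and group belonging". The product of group and time is not written out. The section does not say whether the random effects are intercepts only or whether the effect of time may vary by school.
- **Allocation (opening of Methods).** The two waves are described as "quasi-experimental non-randomized design (wave 1) and cluster-randomized design (wave 2"). In wave 1 the principal's choice decides the group (Recruitment), so the school is the unit there too.
- **Sample size (Participants, repeated in Recruitment).** "62 schools are required, based on an effect size of 0.25 and a power of 80"%, with "12 classes per school, 20 students per class" and "an intraclass correlation (ICC) of 0.10 at school level and 0.05 at classroom level". Class is a level here, and grade is not.
- **Occasions (opening of Methods, Table 1).** Three in wave 1 and two in wave 2, with a baseline in both.
- **Movement between grades (Individual level measures, achievement paragraph).** Wave 1 students who enter in grade 4 or 7 finish in grade 6 or 9.

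**The concern.** In a trial with a baseline, the treatment effect is the difference between groups in change over time. A random intercept for a school describes a difference that stays the same on every occasion, and such a difference drops out of change. A school can also move as a whole between occasions, because of a new head, staff turnover, a local policy, or a different response to the programme. Only a school-by-time term, or a test carried out at school level, recognises that this movement is shared by all students in the school.

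Without one, the standard error of group-by-time is computed as if students had been allocated one by one. It is too small whenever schools change differently. That would undermine the effectiveness claim in the cluster-randomized wave in particular.

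Two smaller points concern the middle level. The trial was sized with a classroom ICC, but the analysis uses grade. And if grade is coded at each occasion, wave 1 students pass through several grades and are not nested in one, as a three-level hierarchy requires.

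**Working it through.** **1. The plan's own figure.** Inputs from Participants: effect size 0.25, power 80%, 12 classes × 20 students = 240 per school, ICC 0.10 (school) and 0.05 (class). Two-sided alpha 0.05 and 1:1 allocation are assumed, since neither is stated.

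V = 0.10 + 0.05/12 + 0.85/240 = 0.1077

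K = 4 × (1.96 + 0.84)² × V / 0.25² ≈ 54.1, so 55 schools. With a t reference on K − 2 degrees of freedom it is 57, or 58 for equal arms. The stated 62 is not reproduced, but it errs on the safe side (power about 84–85%) and does not bear on this point. What matters is that the school component is 0.10/0.1077 = 93% of V: the trial was sized with the school as the effective unit.

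**2. What random intercepts do to change.** Take two occasions and intercepts for school, grade within school, and student. All three are the same before and after, so a student's change is the group's mean change plus the difference of two residuals. The model therefore treats changes as independent between students. With balanced data and N students:

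model SE = √(4 × Var(change) / N)

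This is the two-sample comparison of individual change scores. If change also has a school component, a class component and a person component, the true value is:

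true SE = √[(4/K) × (school + class/12 + person/240)]

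**3. Size by school-level ICC of change.** Call this ICC ρ (assumed, not in the article). With school clustering only:

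(true SE / model SE)² = 1 + 239ρ; type I error = 2 × P(Z > 1.96 / ratio)

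| ρ | 1 + 239ρ | SE ratio | Type I error |
|---|---|---|---|
| 0 | 1.00 | 1.00 | 5% |
| 0.001 | 1.24 | 1.11 | 8% |
| 0.005 | 2.19 | 1.48 | 19% |
| 0.01 | 3.39 | 1.84 | 29% |
| 0.02 | 5.78 | 2.40 | 41% |
| 0.05 | 12.95 | 3.60 | 59% |

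These do not depend on the number of schools. If only 60 students per school were analysed (an assumption), 1 + 59ρ gives 12% at 0.01 and 32% at 0.05.

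**4. The same in terms of stability over time.** Keep the plan's ICCs (0.10, 0.05), 62 schools, and an assumed person-level correlation over time of 0.7. Let school and class effects correlate c between occasions. Components of change: school 2(1 − c) × 0.10, class 2(1 − c) × 0.05, person 2 × 0.3 × 0.85 = 0.51.

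For c = 0.95 these are 0.010, 0.005 and 0.51, total 0.525, so ρ = 0.019. With N = 62 × 240 = 14,880, the model SE is √(4 × 0.525/14,880) = 0.0119. The true SE is √[(4/62)(0.010 + 0.005/12 + 0.51/240)] = 0.0284. The ratio is 2.39 and type I error is 41%.

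Across c = 1.00, 0.98, 0.95, 0.90 and 0.80, type I error is 5%, 25%, 41%, 54% and 65%. At c = 0.95, moving the person-level correlation from 0.5 to 0.8 moves it from 32% to 49%.

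**5. Simulation check.** In 1,500 null trials per setting, generated on the change scale, the student-level test rejected in 4.5%, 41%, 54% and 64% at c = 1.00, 0.95, 0.90 and 0.80. A test on school mean changes with 60 degrees of freedom rejected in 4.5%, 5.1%, 5.2% and 5.5%, with no class term.

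**6. Class alone.** If change clusters by class only (20 students), 1 + 19ρ gives type I error of 7%, 10% and 16% at ρ = 0.01, 0.02 and 0.05. Step 5 shows that clustering change by school already restores the level, so class is secondary.

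**The case against.** The strongest reply is that the section is one paragraph of a journal article. It calls the model a random effect model with time as a predictor and never says intercepts only, so a random slope for time by school is not excluded. Covariance form and degrees of freedom usually belong to an analysis plan. This stands to the extent that the fault is conditional. It does not remove the point: the article chose to list its random effects, varying by three grouping factors is how random intercepts are ordinarily described, and an analyst who followed the list would leave the needed term out.

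Second, the magnitude rests on an ICC of change that nobody has stated, and at zero there is no inflation. That is correct. But the intervention is delivered school-wide, and both the second research question and the Discussion expect school-level factors to moderate its effect. Those are reasons to expect schools to change differently, though not by how much.

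Third, the argument about grade cannot run both ways. Coded at entry, grade cancels from change and students are nested in it. Coded at each occasion, students are not nested and grade does not cancel for those who move. The article does not say which. So exact cancellation is claimed only for wave 2. In wave 1 changing grade complicates the algebra but supplies no school-by-time term.

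Fourth, 12 classes over grades 4–9 is 2 per grade, and over grades 1–9 about 1.3, so grade within school is a fair stand-in for class. This is largely right and is why class is treated as secondary. Nor does the 240-student figure apply to the teacher-reported school-level measures.

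**Conclusion.** The point holds in conditional form. As written, the model names no school-by-time effect and swaps class for grade. Under the ordinary reading of its random effects, the group-by-time standard error ignores school clustering of change. With 240 students per school, type I error runs from 5% if schools change in parallel to 29% at an ICC of change of 0.01 and 59% at 0.05. This assumes random intercepts only, a group-by-time test, two-sided 5%, 1:1 allocation and balanced data.

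A reader might go further and infer that the plan definitely fixes an unclustered test and will give false positives in both waves. The article does not support that: it neither excludes random slopes nor writes the interaction, and it gives no ICC of change. A reader might also suppose that a single teacher rates each whole class, so that a class effect is indispensable. The article speaks only of teacher ratings and does not say how raters are assigned.

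This is still more than missing detail. Following the listed structure gives standard errors that are too small whenever schools change differently, and the wording should be corrected before analysis.

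**What to change.** In the Data analyses section:

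1. Name group-by-time as the treatment effect.
2. Add a random school-by-time term: a random slope for time by school in wave 1, a school-by-occasion effect in wave 2. For wave 2 an alternative is the post score adjusted for baseline, with a random school effect.
3. Base degrees of freedom on the number of schools, for example K − 2 or Kenward–Roger.
4. Secondary: make class the intermediate level, to match the sample-size calculation, with grade as a fixed covariate; or keep grade and say why. In either case state whether grade is coded at entry or at each occasion in wave 1.

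The cost is analysis wording, plus class codes in the data file if class is used. Confidence intervals will be wider where schools change differently, but they will be correct.

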### Recruitment

Information about the study will be distributed by e-mail to all compulsory schools in Sweden. The e-mail lists will be retrieved from Swedish National Agency for Education. In addition, information about the study will be distributed at conferences and via regional principal and teacher networks. School principals and teachers will be invited to online meetings at which detailed information about the study will be presented and detailed information on participation in the study will be provided. Upon enrollment in the project, the information and invitation to participate in the study is distributed to students’ guardians. In addition to Swedish language, information about the study will be presented in ten frequent languages in Sweden (Arabic, Spanish, English, Somali, Serbo-Kroatian, Polish, Kurdish, Finnish, Farsi, and Urdu). Students in grade 9 will also be asked for informed consent, upon consent from both guardians.

In the first wave of recruitment, the decision to allocate participants to intervention or control group will be based on the school principals’ choice of intervention. The schools, catering for students in grades 4–9, which have expressed interest in the intervention, will be stratified in three groups, based on size, parent educational level, proportion of students with migrant background and students’ average achievement rates. This information is publicly available from SALSA database of the National Agency for Education. After stratification, schools within each stratum will be assigned to intervention group. The same procedure will be conducted in the recruitment of control groups. In the second wave of recruitment, the participants from schools grades 1–9 will be recruited the study, and then randomly allocated to either intervention or control group.

According to estimations with the software Optimal Design (OD; Spybrook et al., 2011), 62 schools are required, based on an effect size of 0.25 and a power of 80% with an expected amount of 12 classes per school, 20 students per class and an intraclass correlation (ICC) of 0.10 at school level and 0.05 at classroom level (Hedges & Hedberg, 2007). To account for 20% attrition, 74 schools are needed (approximately 17 280 students). Therefore, in each wave of data collection, a minimum of 74 schools will be recruited.

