### Individual level measures

At individual level measures constitute teacher ratings of students’ social-emotional skills, behavior problems and academic competence, using Social Skills Improvement System – SEL Brief and Mental Health Scales, Teacher K-12 Form [33] as well as teacher and student questionnaires of classroom learning climate [32, 34].

**Social emotional skills.** Social Skills Improvement System – SEL Brief and Mental Health Scales, Teacher K-12 Form [33] contains 20 items related to five competency domains (self-awareness, self-management, social awareness, relationship skills, and responsible decision making) and 10 items encompassing emotional behavior concerns (internalizing and externalizing concerns). Examples of items are “Asks for help when needed” for social-emotional skills competency domains and “Withdraws from others” for emotional behavior concerns. The items are measured on a 4-point scale (1 = Never, 2 = Seldom, 3 = Often, 4 = Almost always). The measures have proved to have sufficient validity and reliability in previous studies [35, 36].

**Classroom learning environment.** A comprehensive assessment of the classroom learning environment is conducted using questionnaires for teachers and students [32, 34]. The teacher questionnaire consists of 14 statements, rated on a 4-point scale (1 = does not fit to 4 = fits completely), assessing various aspects of the classroom learning climate. The student questionnaire includes 22 statements, also rated on a 4-point scale, gauging students’ perceptions of the classroom environment. An example of an item in the teacher questionnaire is “There is a good working climate during lessons”. An example of an item in the student questionnaire is “Students in this class are active and interested during lessons”.

**Students’ achievement.** In addition, for the first wave of recruitment, students’ achievement on national tests of Swedish and mathematics will be retrieved from register data provided by Statistics Sweden. The data will be standardized across tests and compared with regard to the national average for those students who enter the project in grade 4 and 7 (national tests in grade 3 and grade 6) and finish the project in grade 6 and 9 (national tests in grade 6 and grade 9).

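### Imputation is made conditional on data being missing completely at random, which is the wrong condition, and no method is given if it fails

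*Protocol article*

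**What the plan says.** The missing-data rule is one sentence at the end of Data analyses: "Missing data will be handled by imputation, provided that the assumption of data missing completely at random is met". Nothing follows for the case where the assumption is not met, and MAR is not mentioned anywhere in the article.

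The same section plans a "three-level random effect model will be used, varying by school, grade and the individuals’ identification codes", with outcomes studied over time ("three time points for wave 1 and two time points for wave 2") and by group. It also plans analyses of implementation quality as a mediator and of school characteristics and school-level variables as moderators. It does not say whether students with incomplete records stay in the model.

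On expected loss, Participants says: "To account for 20% attrition, 80 schools are needed". The opening of Methods and the Discussion both give the difficulty of holding a control group over two years as the reason for having two waves. On grades, Recruitment describes the wave 1 schools as "catering for students in grades 4–9". Table 1 puts the wave 1 measurements in 2023, 2024 and 2025. For the national tests, Individual level measures describes the cohorts in question as follows: "enter the project in grade 4 and 7 (national tests in grade 3 and grade 6) and finish the project in grade 6 and 9".

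**The concern.** The rule permits imputation where there is no bias to remove and withholds it where observed data could remove bias. This is a commitment stated wrongly, not detail left to a fuller document: an analysis plan that followed the sentence would inherit the error.

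It matters because the plan itself gives reasons to doubt MCAR. If the check fails and the analysts then drop incomplete records, and if loss is selective in different ways in the two arms, the group-by-time effect is biased. That effect is the study's main quantitative result, and the effect expected is small (Cohen's d of 0.20 in Participants).

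**Working it through.** The plan gives no figure for this point, so there is nothing to reproduce. Three checks follow.

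**1. What each assumption buys.**

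| Missingness | Complete cases | Imputation from observed variables |
|---|---|---|
| MCAR | unbiased | unbiased; gains precision only |
| MAR | can be biased | unbiased if the right variables are in the model |
| Not at random | can be biased | can be biased; needs sensitivity analysis |

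The plan allows imputation in the first row only. The second row is the one for which imputation is designed.

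**2. Is MCAR plausible in wave 1?** Inputs: grades 4–9 (Recruitment), three yearly measurements (Table 1), and a rise of two grades from first to last measurement (4 to 6 and 7 to 9, Individual level measures). A student entering in grade g is still in compulsory school at the third point only if g + 2 ≤ 9, so g ≤ 7. If all grades are enrolled:

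- entrants in grade 9 (1 of 6 grades, 17%) are gone by the second point;
- entrants in grades 8 and 9 (2 of 6 grades, 33%) are gone by the third.

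The percentages assume grades of equal size. Missingness would then depend on grade, so it would not be MCAR for any outcome that varies with grade. Since grade is observed and already in the planned model, this part of the loss is compatible with MAR. The 33% is a share of grades, not a measure of bias.

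**3. Possible size of bias with complete cases.** All inputs here are assumed, apart from the 20% loss and the 0.20 effect, which are the plan's figures. The plan applies its 20% to the number of schools; applying it to students in one arm is an assumption. Scores have SD 1, the baseline–follow-up correlation is 0.6, there is no clustering, and one arm loses exactly its lowest 20% at baseline while the other loses nobody.

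- Mean baseline of the remaining 80%: normal density at the 20th percentile divided by 0.80 = 0.280 / 0.80 = 0.35.
- Shift in that arm's follow-up mean: 0.6 × 0.35 = 0.21.
- Shift in the group-by-time effect: follow-up shift minus baseline shift = 0.21 − 0.35 = −0.14 SD.

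With a true effect of 0.20, completers would show 0.20 − 0.14 = 0.06. A loss half as selective halves the shift: 0.175 × 0.6 − 0.175 = −0.07 SD. The sign depends on which arm loses which students.

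A simulation of the extreme case (8,000 students per arm, true group-by-time effect 0.20) agrees. A random-intercept model gave 0.06 on completers and 0.20 (standard error 0.015) on all available records.

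A second simulation looked at the follow-up difference between arms, with a true difference of 0.25 and about 20% missing:

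| Loss depends on | Completers | Imputation under MAR | Baseline-adjusted model, observed data |
|---|---|---|---|
| nothing (MCAR) | 0.25 | 0.25 | 0.25 |
| baseline, same in both arms | 0.25 | 0.25 | 0.25 |
| baseline, in one arm only | 0.35 | 0.25 | 0.25 |
| baseline, opposite directions by arm | 0.46 | 0.25 | 0.25 |

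Bias appears only where selective loss differs by arm. Imputation under MAR and the baseline-adjusted model both remove it there.

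**The case against.** The strongest objection is that the planned model may already do most of what is needed. A random-effects model fitted by likelihood to repeated records ordinarily keeps every observed time point and is valid under MAR for missing outcomes without any imputation. A reader might infer from the rule that the analysis falls back on complete cases; the article does not say so. This objection stands for outcomes. It does not cover missing covariates, moderators or the fidelity mediator, and the article does not say that incomplete records are kept.

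A reader might also infer that MCAR fails by design in wave 1. The text does not go that far. The two-grade progression is given only for the national tests and only for entry in grades 4 and 7. Recruitment describes which grades the schools serve; it does not say that entrants in grades 8 and 9 are followed for two years. Leaving after grade 9 would also occur in both arms. Nor does allocation by principals' choice make data non-MCAR: it makes the groups non-equivalent, which is a separate matter. Wave 2, with two measurements in one school year, is not touched by the two-year grade argument.

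Finally, 0.21 SD could be read as the bias in the treatment effect. It is the shift in one arm's follow-up mean; the matching group-by-time shift is −0.14 SD, and the scenario behind it is deliberately extreme. Nothing in the article shows that loss will be selective in one arm only.

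None of this rescues the condition itself, which is wrong whatever the pattern of loss turns out to be.

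**Conclusion.** The rule is wrong as written and should be replaced. MCAR is not the condition that imputation needs, it is doubtful given the attrition and retention problems that the plan foresees, and nothing is specified if it fails.

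The harm is conditional. It requires complete-case fitting, or incomplete covariates, moderators or mediators, together with loss that is selective and differs by arm. Under the assumed extreme case the completer group-by-time effect moves by about 0.14 SD in size, against an expected 0.20; with half the selectivity, by about 0.07 SD. With equal loss in both arms, or a likelihood fit to all observed records under MAR, bias in the outcome comparison is essentially nil in these illustrations. The documents do not support the stronger claims that MCAR is certain to fail or that the plan commits to complete cases.

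**What to change.** Replace the sentence in Data analyses with text that does the following:

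- deletes the MCAR condition and states MAR given observed variables as the primary assumption;
- fits the planned mixed model by maximum likelihood to all observed time points, with grade and school variables included;
- uses multilevel multiple imputation, including arm, grade, school and baseline, for missing items, covariates and mediators;
- adds a sensitivity analysis for departures from MAR;
- states that scores are not imputed for time points after a student has left compulsory school.

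The last item also settles how any wave 1 entrants in grades 8 and 9 contribute: up to the time points they can reach. The cost is one paragraph of text and modest extra analysis work. No new data are needed and the sample size does not change.
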